## 4 Outcome

### 4.1 Primary outcome

The treatment efficacy rate, defined as a reduction of ≥50% in the numeric rating scale (NRS) score at 3 months post-treatment compared to the pre-treatment score, will be evaluated as primary outcomes.

### 4.2 Secondary outcome

#### 4.2.1 Clinical symptom assessment indicators

Short Form 12 (SF-12): evaluates the patient's quality of life.

Athens Insomnia Scale (AIS): assesses the patient's sleep condition.

Beck Depression Inventory (BDI): evaluates the patient's psychological improvement.

Michigan Neuropathy Screening Instrument (MNSI): assesses the improvement of diabetic peripheral neuropathy.

#### 4.2.2 Clinical examination assessment indicators

Before enrollment, assessments of glycated hemoglobin (HbA1c), insulin levels, and C-peptide levels are conducted to evaluate changes in the primary disease, diabetes. Additionally, bilateral lower limb infrared thermography will be performed preoperatively, at 2 weeks postoperatively, and at 3-month follow-up to assess microcirculatory function. All scans will be conducted in a dedicated temperature-controlled examination room, with the device maintained at ~1 meter from the subject and the temperature range set at 25°C−40°C to ensure optimal thermal imaging quality. Patients are also instructed to record their concurrent use of analgesic medications.

## 5 Safety evaluation

Routine blood tests, liver and kidney function tests, electrocardiograms (ECG), and X-ray imaging are performed at screening period (visit 1) and at the 2-week follow-up post-operation (visit 2). At the 3-month follow-up post-operation (visit 3), the patient's vital signs (blood pressure, heart rate, body temperature, and respiration) and physical examination are assessed. If abnormalities are detected during follow-up, the patient's clinical manifestations should be evaluated by a relevant specialist. If confirmed to be caused by the study, it should be documented as an adverse event, and appropriate treatment should be provided. Additionally, any complications related to the study (e.g., infection, cerebrospinal fluid leak, pneumothorax, electrode fracture) should be documented as adverse events, and appropriate treatment should be administered. During the trial, any serious adverse events will be promptly reported to both the medical device clinical trial administration department and the ethics committee. The study will be suspended if the trial places participants at immediate risk of life-threatening conditions or if the incidence of serious adverse events significantly exceeds expectations.

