## Abstract

**Background:**

Diabetic peripheral neuropathic pain (DPNP), affecting ~50% of diabetes patients, imposes major burdens on quality of life and healthcare systems, while current therapies including pharmacotherapy and conventional spinal cord stimulation remain limited by insufficient efficacy and adverse effects. Our study aims to evaluate the clinical efficacy and safety of 10 kHz high-frequency spinal cord stimulation (HF-SCS) compared to traditional low-frequency SCS (T-SCS) in alleviating DPNP.

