**Methods:**

This prospective, randomized, controlled, multicenter trial will enroll 100 participants with DPNP. Patients aged 18–80 with chronic (≥6-month) lower limb pain will be randomly assigned to HF-SCS (10 kHz) vs. T-SCS (40–60 Hz). The primary outcome is the treatment efficacy rate, defined as ≥50% reduction in numeric rating scale (NRS) scores at 3 months post-intervention. Secondary outcomes include improvements in quality of life (Short Form 12), sleep quality (Athens Insomnia Scale), psychological status (Beck Depression Inventory), neuropathy severity (Michigan Neuropathy Screening Instrument), and microcirculatory parameters assessed via infrared thermography. Safety evaluations encompass adverse events, laboratory tests, and imaging findings.

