### 2.5 Criteria for discontinuation

During this trial, subjects experiencing the following conditions will be considered as dropout cases, and the reason and date of dropout will be recorded in a case report form.

(1) Violation of inclusion/exclusion criteria at enrollment, with the investigator determining compromised participant safety.(2) Participant intolerance to the treatment regimen.(3) Adverse event (AE) occurrence leading to investigator-determined unsuitability for continued study treatment.(4) Major protocol deviations (e.g., non-compliance with study procedures) affecting safety or efficacy assessments.(5) Pregnancy.(6) Withdrawal of informed consent: if a participant withdraws consent; the investigator must document the scope of withdrawal (e.g., discontinuation of treatment only vs. withdrawal from all study procedures/follow-ups) in medical records.(7) Loss to follow-up: defined as failure to attend visits and inability to contact the participant despite ≥2 documented contact attempts at ≥1-week intervals.(8) Early termination of study treatment: discontinuation of treatment while continuing study procedures/follow-ups (if applicable).(9) Early study withdrawal: complete discontinuation of all study-related activities, including treatment and follow-ups (e.g., due to consent withdrawal or loss to follow-up).(10) Follow-up for AE/SAE-related withdrawals: participants withdrawing due to treatment-emergent adverse events (TEAEs) or serious adverse events (SAEs) must be followed until resolution (return to baseline/stable status) or until the AE is deemed clinically insignificant by the investigator.

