### 2.6 Randomization and blinding

Competitive enrollment will be conducted across centers. An independent statistician at each center will perform centralized randomization using a validated centralized randomization system. Participants will be randomly assigned to either the HF-SCS group or the T-SCS group at a 1:1 allocation ratio, based on a computer-generated random number.

Due to the distinct sensory profiles between HF-SCS and T-SCS, effective blinding of participants and outcome assessors was not feasible; therefore, only data statisticians were maintained under blinded conditions throughout the study.

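### Section 5 makes causation by the study the condition for documenting an adverse event, which conflicts with Table 1 and Section 2.5 and leaves the comparison of non-serious events under-counted and open to differential attribution

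*Protocol article*

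**What the plan says.** Section 5 (Safety evaluation) of the protocol article describes two ways in which something becomes a documented adverse event.

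- Abnormal findings: "If abnormalities are detected during follow-up, the patient's clinical manifestations should be evaluated by a relevant specialist". The next sentence sets the condition: "If confirmed to be caused by the study, it should be documented as an adverse event".
- Complications: "any complications related to the study (e.g., infection, cerebrospinal fluid leak, pneumothorax, electrode fracture) should be documented as adverse events".

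The same section treats serious events differently: "any serious adverse events will be promptly reported to both the medical device clinical trial administration department and the ethics committee". That sentence has no causality condition.

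Three other places bear on the point.

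- Table 1 marks adverse events for collection at Visit 1 (Day −7 to 0), Visit 2 (Day 14 ±5) and Visit 3 (Day 90 ±7), without reference to cause.
- Section 2.5, item 10: "participants withdrawing due to treatment-emergent adverse events (TEAEs) or serious adverse events (SAEs) must be followed until resolution".
- Section 2.6, on blinding: "only data statisticians were maintained under blinded conditions throughout the study".

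The abstract states a comparative aim that covers safety as well as efficacy, and its Methods paragraph adds: "Safety evaluations encompass adverse events, laboratory tests, and imaging findings".

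**The concern.** Relatedness is normally an attribute graded on an event that has already been recorded. Section 5 puts the grading first, and documentation depends on its outcome. No route is given for a non-serious event judged unrelated or of uncertain cause, and no criteria are given for what counts as confirmation.

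This matters because safety is part of the comparison between arms. Randomisation protects a comparison of all-cause event rates. It does not protect a comparison of events that have been filtered, after allocation, by a judgement made with the arm known. Blinding the statisticians does not help, since they cannot analyse events that were never entered. Centres may also differ: one that works from Table 1 and one that works from Section 5 would record different sets of events.

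**Working it through.** The protocol states no figure on this point, so there is none to reproduce. The check has two parts.

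**1. The passages side by side**

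- *Section 5 against Table 1.* Visit 1 lies before or up to the day of the operation. Nothing found then can have been caused by the operation or the stimulation, yet Table 1 collects adverse events at that visit. A strict causality condition would leave that entry with almost nothing to hold.
- *Section 5 against Section 2.5.* Treatment-emergent, in its usual sense, is a matter of timing: an event that begins or worsens after treatment starts. The article does not define the term otherwise. Section 5 uses cause instead.
- *Section 5 against itself.* Serious events are reported whatever their cause, while abnormalities and complications are documented according to cause.
- *Section 5 with Section 2.6.* Blinding is confined to statisticians. No masking is described for the specialist who evaluates abnormalities.

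**2. Illustration of size (assumed rates)**

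The only input from the documents is 50 patients per arm (Sections 2.1 and 2.2). Event rates and attribution fractions are assumptions. For true rate p and attributed fraction q, the expected number recorded is 50 × p × q.

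Same true rate in both arms, p = 30%, so 50 × 0.30 = 15 patients with an event per arm:

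- 50% attributed in each arm: 15 × 0.50 = 7.5 versus 7.5. There is no false difference, but half the events are lost.
- 70% versus 50%: 10.5 versus 7.5, a false difference of 0.30 × (0.70 − 0.50) = 6 percentage points.
- 80% versus 40%: 12 versus 6, a false difference of 0.30 × (0.80 − 0.40) = 12 percentage points.

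Real difference of 40% versus 20%, with the same attributed fraction in both arms. Power is for a two-sided 0.05 test of two proportions (normal approximation, pooled variance under the null):

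- 100% attributed: 40% versus 20%, power about 59%.
- 70%: 28% versus 14%, about 40%.
- 50%: 20% versus 10%, about 29%.
- 30%: 12% versus 6%, about 18%.

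So unequal attribution can create a difference that does not exist, and equal attribution makes a real one harder to see.

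**The case against.** The strongest reply is that Section 5 does not contain the word only. The conditional sentence tells sites when an abnormal finding must be called an adverse event; it does not say that nothing else is recorded. Table 1 and Section 2.5 carry no causality condition, and a condensed article may leave the full definition and the relatedness field to the full protocol and CRF. This stands in part: the article does not prove that the database will hold attributed events alone. It does not remove the point. The article states a rule rather than staying silent, both of its routes depend on a link to the study, and no sentence elsewhere overrides it.

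A reader might infer several stronger conclusions that the documents do not support.

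- *That the suspension rule would run on a filtered count of serious events.* Section 5 has any serious event reported, without a causality condition. Filtering would follow only if the condition for abnormalities were carried into the definition of a serious event, which the text does not do.
- *That event rates by arm could not be recovered at all.* Laboratory tests, ECG and X-ray are scheduled for every participant at Visits 1 and 2, and vital signs and physical examination at all three visits. Rates of abnormal results can be computed from these whatever label is applied. What may be lost is narrower: non-serious clinical events judged unrelated or uncertain.
- *That the specialist is known to be unblinded.* This is an inference from Section 2.6, which does not mention that role. It is a reasonable inference, not a stated fact.
- *That a safety difference of a given size or direction will result.* Both arms have the same operation and the same 10–14 days with the electrode in place, and nothing in the article shows that attribution would differ by arm.

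**Conclusion.** The point holds within limits. Section 5 states a recording rule conditioned on causation or relatedness, and that rule does not fit Table 1 or Section 2.5. Followed as written, it would under-count non-serious clinical events and expose their comparison to differential attribution. This rests on two readings: that the conditional sentence works as a gate, which is its natural sense, and that the causality judgement is made with the arm known. Neither the size nor the direction of any bias can be determined from the documents; the figures above show only what assumed rates would do. The primary outcome, the sample size and the planned χ² test are unaffected. This is a should-fix, and it needs to be settled before events accrue, because unrecorded events cannot be reliably reconstructed later.

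**What to change.** Reconcile Section 5, Table 1 and Section 2.5 under one recording rule. Suggested wording: *Every untoward medical occurrence from Visit 1 through Visit 3 (Day 90 ±7), including clinically significant changes in laboratory tests, ECG, imaging, vital signs or physical examination, is recorded as an adverse event irrespective of cause. Relatedness to the procedure, device or stimulation is then graded in a separate CRF field.*

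The window is the one already in Table 1. Ending at Day 90 exactly, or starting at the operation, would narrow it, since Visit 3 can fall as late as Day 97 (90 + 7).

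Report all-cause adverse events and serious adverse events by arm first, and related events second. The order matters: relatedness may still be graded by people who know the arm, so the related-event comparison remains open to differential attribution while the all-cause comparison does not depend on that grading. No change to the suspension rule is proposed.

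The cost is one revised protocol sentence, one CRF field, slightly more event recording, and a higher adverse event count.

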## 6 Statistical analysis

Primary evaluation indicator, the treatment efficacy rate is expressed as the percentage of patients with effective treatment. Between-group comparisons are conducted using the χ^2^ test. Secondary Evaluation Indicators, including the scores of the various scales mentioned above and the values of clinical test items, expressed as mean ± standard deviation. For normally distributed data with equal variance, an independent sample *t*-test is used. For data that are not normally distributed or have unequal variance, the rank-sum test is applied. All data are analyzed using SPSS 26.0 statistical software, with a significance level of *P* < 0.05 considered statistically significant.

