### 2.2 Sample size

According to the results of RCT studies comparing HF-SCS with traditional SCS for the treatment of PDPN, the efficacy rate of HF-SCS for PDPN is ~86%. Based on the statistical sample size calculation method for superiority trials, with a one-sided significance level (α) of 0.025, a test power (1-β) of 0.8, and an equal sample size ratio between the treatment group and the control group, the required sample size for each group was calculated using PASS 17.0 to be 45 cases. Considering a 10% loss to follow-up and refusal rate, at least 50 cases are needed in the treatment group and 50 cases in the control group, resulting in a total sample size of 100 cases.

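### Secondary outcomes are tested without a baseline term, and unequal variances go to a rank-sum test that does not address the means reported

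*Protocol article*

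**What the plan says.** Section 6 sets out the secondary analysis in three steps.

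- **Summary:** the secondary indicators are described as "including the scores of the various scales mentioned above and the values of clinical test items, expressed as mean ± standard deviation".
- **First test:** "For normally distributed data with equal variance, an independent sample" t-test is used.
- **Alternative test:** "For data that are not normally distributed or have unequal variance, the rank-sum test is applied".

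The threshold is given as "with a significance level of *P* < 0.05 considered statistically significant", without saying whether it is one- or two-sided. No covariate is named.

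Table 1 schedules SF-12, AIS, BDI, MNSI and infrared thermography at screening and at both follow-up visits, so each has a baseline value. Section 4.2.1 describes one of them in terms of change: "Michigan Neuropathy Screening Instrument (MNSI): assesses the improvement of diabetic peripheral neuropathy". The abstract likewise speaks of improvements in the secondary outcomes. Section 6 speaks only of scores and values, and does not say whether the follow-up value or the change from baseline is tested.

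**The concern.** There are two faults, both in what Section 6 states.

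**Baseline is collected but not used as a covariate.** The two-sample tests named leave two possibilities. Comparing follow-up scores ignores baseline. Comparing change scores subtracts it with a fixed coefficient of 1, whatever the correlation. Adjusting for baseline by regression has a smaller residual variance than either, at no cost in data.

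**The unequal-variance rule changes the question.** When spreads differ, the rank-sum test responds to whether values in one arm tend to exceed those in the other. That is not the difference in means, so the p-value and the displayed mean ± SD would answer different questions, and no effect estimate would link them.

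These outcomes carry weight in the article. Participants and assessors are unblinded (Section 2.6), Section 8 relies on thermography as an objective complement, and Section 7 ties adoption of HF-SCS to significant gains in symptoms, quality of life and microcirculation.

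**Working it through.** **Inputs from the document.** Section 2.2 gives 45 evaluable per group. Allowing 10% loss, 45 / (1 − 0.10) = 50, which reproduces the planned 50 per group. That size was set for the primary outcome, and no figure is stated for any secondary outcome. It is used here only as the number available.

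**Assumptions.** The document gives none of the following, so ranges are shown: a true difference of 0.5 SD; baseline–follow-up correlation r of 0.3, 0.5 and 0.7; equal SDs at baseline and follow-up; SD ratios between arms of 1 to 3; a two-sided 5% level.

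**Step 1: precision.** In units of the follow-up variance, the variance of the compared quantity is:

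- follow-up score: 1
- change score: 2(1 − r)
- ANCOVA: 1 − r²

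Since 2(1 − r) − (1 − r²) = (1 − r)² ≥ 0, ANCOVA is never less precise than the change score. It is never less precise than the follow-up score either, apart from one degree of freedom. Power comes from the noncentral t distribution with noncentrality (0.5 / √variance) × √(45/2). For the follow-up score this is 0.5 × 4.743 = 2.37.

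| r | Change variance | ANCOVA variance | Power, follow-up | Power, change | Power, ANCOVA |
|---|---|---|---|---|---|
| 0.3 | 1.40 | 0.91 | 65% | 51% | 69% |
| 0.5 | 1.00 | 0.75 | 65% | 65% | 77% |
| 0.7 | 0.60 | 0.51 | 65% | 86% | 91% |

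A normal approximation gives values up to one point higher. At r = 0.5, ANCOVA with 45 per arm is worth about 45 / 0.75 = 60 per arm on follow-up scores alone.

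**Step 2: rejection rate when the means are equal.** Simulation with 40,000 runs per setting, 45 v 45, nominal 5%. The skewed case is a gamma distribution with shape 2, centred to a common mean.

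| SD ratio | Normal: rank-sum | Normal: Welch | Skewed: rank-sum | Skewed: Welch |
|---|---|---|---|---|
| 1 | 4.8% | 5.1% | 4.8% | 4.8% |
| 1.5 | 5.1% | 5.0% | 11.5% | 5.1% |
| 2 | 5.7% | 4.9% | 19.7% | 5.5% |
| 3 | 6.8% | 5.0% | 27.3% | 5.4% |

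Separate runs of the skewed case gave about 11% and 19% at ratios 1.5 and 2, so the first decimal should not be read closely. The large distortion needs skew and unequal spread together; neither alone produces it here.

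**Step 3: unequal arms, normal data.** With 50 v 40 and the larger SD in the smaller arm, rank-sum gives 5.8%, 6.6% and 8.1% at ratios 1.5, 2 and 3. With the larger SD in the larger arm it gives 4.9%, 4.8% and 5.5%. The direction therefore matters.

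**Step 4: is the switch needed?** At 45 v 45 on normal data, the ordinary t-test stays at 5.0% to 5.2% across all SD ratios. At the planned allocation, moving to rank-sum for unequal variance alone protects against nothing.

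**The case against.** The case on the other side is substantial, and several parts of it stand.

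- **Follow-up scores are not stated.** A reader might infer that raw follow-up scores are compared with baseline ignored. The references to improvement leave change scores open, so the document does not establish this. What stands is that the choice is unstated and that ANCOVA is more precise either way.
- **Unadjusted tests are valid.** In a randomised trial they cost precision, not validity, and at r = 0.3 the gain over follow-up scores is only about 4 points of power.
- **An article condenses, and an unseen SAP may say more.** That covers what is absent. Section 6, however, does name the tests, and a SAP that followed it would carry the choice forward.
- **The error rate is usually close to nominal.** A reader might infer that the rank-sum rule generally inflates type I error. With near-normal data and balanced arms it does not, up to an SD ratio of about 2. The test is also valid under its own null of identical distributions, and Section 6 does not state the null as equal means.
- **Pre-testing.** A reader might blame the data-driven choice of test. Modelled as a Levene test followed by t-test or rank-sum, the rule gives 5.0/5.1/5.7/6.8% on normal data, against 4.8/5.1/5.7/6.8% for rank-sum alone. With unequal spread and skewed data it is equal or lower (6.6/18.1/27.3% at ratios 1.5, 2 and 3). Pre-testing adds almost nothing.
- **NRS as a continuous secondary outcome.** Its absence from Section 4.2 is a design choice, not an error.

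**Conclusion.** The point holds in two limited parts, both confined to the secondary outcomes.

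First, Section 6 names tests with no baseline term and leaves the compared quantity undefined. Under the assumptions above, ANCOVA gains about 4 to 26 points of power over follow-up scores (69 − 65 to 91 − 65) and about 5 to 18 over change scores (91 − 86 to 69 − 51).

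Second, sending unequal variances to the rank-sum test is poorly chosen, because it separates the p-value from the means displayed. The effect on the rejection rate under equal means is small for near-normal, balanced arms (about 6% at SD ratio 2 and 7% at ratio 3). It can be large with skewed data (about 11% and 19% at ratios 1.5 and 2), while Welch stays near 5%. Bounded scales such as BDI and AIS may be skewed, but the document gives no distributions, so how far this would occur in the trial is unknown.

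The effect size, correlations, SD ratios and gamma shape are all assumptions. This should be corrected, but it does not threaten the primary result.

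**What to change.** In Section 6, replace the t-test/rank-sum rule for the continuous secondary outcomes with the following:

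- Analyse SF-12, AIS, BDI, MNSI and thermography each by ANCOVA of the follow-up value on arm and baseline value, with heteroscedasticity-robust standard errors.
- Report the adjusted mean difference with its 95% confidence interval.
- If a two-sample test is kept, state whether it is applied to follow-up or change scores, and use Welch's t-test where variances may differ.
- Keep the rank-sum test as a sensitivity analysis.

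The cost is a change of wording in the protocol and in any SAP. The baseline values are already scheduled in Table 1, ANCOVA is available in the software named in Section 6, and no new data, visits or participants are needed.
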